## Background

### Antibiotic resistance

Multi-resistant bacteria (MRB) is one of the major threats to the public health(1). In Denmark, the incidence of MRB is increasing (2) and every 20th patient in the Emergency Department (ED) in Denmark is a carrier of MRB(3).

Denmark has focused on this challenge (4) by screening special groups for MRB (5, 6), and initiating campaigns to reduce antibiotic consumption mainly by reducing the use of broad-spectrum antibiotics in hospitals (4, 7).

The Danish Ministry of Health has made extensive efforts targeting the use of antibiotics in hospitals by establishing learning and quality teams (LQT). The experience from LQT identified the major obstacle in reducing the prescription of broad-spectrum antibiotics was insufficient knowledge concerning *if* the patient had a bacterial infection, *where* the infection was located and which kind of bacteria were involved in the infection.(8) Uncertainty in the answer to these three questions often leads a clinician to choose a broad-spectrum antibiotic at the onset of treatment. Unfortunately, often the prescription of a broad-spectrum antibiotic is rarely revised when laboratory results are available, mainly because the patient has often already been discharged(9).

### Acute infections and diagnostic tools

The most common conditions among ED patients with suspected infection are community acquired pneumonia and acute pyelonephritis (defined in this study as an infection above the bladder i.e. pyelitis, nephritis, renal abscess and pyonephrosis) (10, 11). Pneumonia and acute pyelonephritis are urgent infections, and antibiotic treatment should be initiated within a few hours to avoid serious complications such as bacteremia, sepsis, organ failure, septic shock and death (12). A prerequisite for the appropriate use of antibiotics is timely access to accurate diagnostic tests. Diagnosis of pneumonia and acute pyelonephritis is challenging as symptoms are often weak and nonspecific and the current methods for focal and etiological diagnosis have low sensitivity and specificity and often deliver results after the antibiotic treatment decision has been made (9, 13, 14).

The COVID-19 pandemic has highlighted this problem. Quick and correct classification of pneumonia as COVID-19, another viral or bacterial pneumonia, or even COVID-19 complicated with bacterial pneumonia, is of vital importance when selecting the correct treatment (including antibiotics), and the correct isolation and infection control measures.

In order to make the correct diagnosis and prescribe a targeted, appropriate treatment within a few hours of admission, it is important to the physician to be able to answer the following three questions: a) Is it an infection that requires antibiotic treatment (*infection marker*)? b) Where is the infection located (*focal diagnosis*)? c) Which bacteria should the prescribed antibiotic treat (*etiologic diagnosis*)?

### Infection marker

To diagnose an infection, a systemic response to the infection is required: abnormal temperature, increased leucocyte count or neutrocytosis, or elevated C-reactive protein (CRP). There is some uncertainty associated with CRP because it has a delayed response to bacterial infection and often is elevated in non-infectious inflammatory conditions(15). A more sensitive and specific marker is required that can differentiate between bacterial and viral infection and can reflect the severity of the infection(16). Serum Procalcitonin (PCT) has potential as a diagnostic tool in suspected bacterial infection(17) and can distinguish between viral and bacterial pneumonia(18). SuPAR (soluble urokinase plasminogen activator receptor) might have a potential as a marker for acute bacterial infections requiring antibiotic treatment. However, there are no well-conducted studies which compare these three biomarkers diagnostic abilities for bacterial infections in general or in relation to diagnosis of pneumonia and acute pyelonephritis(16, 19).

The abundant and restricted expression of surfactant protein D (SP-D) within the lung makes this protein a specific marker for lung disease(20). Krebs von den Lungen-6 (KL-6) is expressed in the lung and is a diagnostic and prognostic marker of interstitial lung disease(21-24). The inflammatory glycoprotein YKL-40 is associated with severity of interstitial lung disease(25). The value of these lung injury markers for diagnosing pneumonia needs further investigation.

### ***b) Focal diagnostics***

The diagnosis of pneumonia is primarily based on clinical symptoms and findings, supplemented with chest X-ray, which has a low sensitivity and specificity in the diagnosis of pneumonia (26). Identifying an improved imaging alternative with high diagnostic sensitivity and specificity and minimal risk to the patient is imperative. High-resolution CT scan (HRCT) provides a detailed diagnosis of thoracic diseases, but the radiation dose is high and potentially harmful. Low-dose CT scan has shown promising diagnostic results, but the radiation dose is still potentially harmful(27). Ultralow dose CT scan of the thorax (ULDCT) could be an alternative but has yet to be studied within an ED context. Ultrasound scanning (US) of the lungs is useful to diagnose pulmonary edema and pleural effusion, but its value for diagnosing pneumonia needs further investigation(28).

Currently, there are no readily available imaging methods to verify the diagnosis of acute pyelonephritis. The diagnosis is primarily based on unspecific clinical findings (29), and is often not confirmed microbiologically (30). Complicating factors such as hydronephrosis/pyelonephrosis and renal abscess can be visualized with conventional US (31). Contrast enhanced US (CEUS) and US with Doppler and spectral-assessment seems to be promising diagnostic imaging modalities of acute renal inflammation (32, 33). The value and suitability in a clinical setting of these more advanced US investigations are unknown.

### ***Etiological diagnostics***

Sputum can be cultivated to determine a specific bacterial infection. However, results are often first available after discharge of the patient or completion of treatment (9, 16). Therefore, better and faster methods are required. A so-called 'point-of-care' (POC) tool providing rapid microbiological results on e.g. sputum samples would be beneficial. Systems are available today based on PCR (polymerase chain reaction) methods with results available within one hour for a variety of viral and bacterial agents (34). The impact of such systems has not been investigated in an ED context.

The diagnosis of acute pyelonephritis is verified by significant bacteriuria (30), but up to half of the patients with clinical pyelonephritis fails to meet this diagnostic criterion. Unfortunately, the sample to result time for urine cultures are at last one day if negative – two to three days if positive. (29, 30, 35, 36) Urine test strips are unreliable with low specificity and low predictive values (37). Therefore, a POC tool is necessary, which can provide rapid results and quickly identify the many patients who do not have bacteria in the urine. One tool is urine flow cytometry, which has shown promising diagnostic value with a high negative predictive value for the exclusion of bacteriuria (38). However, better documentation for its use as an ED diagnostic screening method is vital.

### ***Hypothesis, aim and objectives***

Our broad hypothesis is that by improving the knowledge of ED infected patients and by introducing new diagnostic tools, which contribute to the development of rapid and more accurate diagnosis of acute infections, a more appropriate antibiotic therapy can be administered.

The project aims to adapt and evaluate alternative diagnostic tools and working methods that support a prompt and accurate diagnosis of hospitalized patients suspected of an urgent infection – with special focus on pneumonia and acute pyelonephritis.

The research objectives are:

- 1) What is the patient characteristics and course of treatment of the different ED infections?
- 2) What is the diagnostic value of the infection markers PCT, suPAR, and CRP in patients with suspected pneumonia and pyelonephritis?
- 3) What is the diagnostic value of the lung injury markers SP-D, YKL-40, and KL-6 on diagnosing pneumonia
- 4) What is the impact of bedside-US and ULDCT on diagnosing pneumonia ?
- 5) What is the impact of advanced US on diagnosing pyelonephritis?
- 6) What is the impact of bedside-US on diagnosing hydronephrosis?
- 7) What is the impact of POC-PCR analysis of sputum on antibiotic prescriptions?
- 8) What is the impact of POC urinary flow cytometry on diagnosing and excluding bacteraemia?

The goal is to combine the results of all these eight objectives into one novel diagnostic model which the ED physician can apply when patients with suspicion of an infection is admitted.

## Method

### Study design

The study is designed as a multifaceted multicenter diagnostic study, where participants are offered additional diagnostics depending on the suspected focus of infection (Figure 1).

The study protocol was reported in accordance with the SPIRIT (Standard protocol items: Recommendations for interventional trials) statement(39).

[figure not shown]

Figure 1 Design of patient flow

## Setting

The study will recruit patients from here regional hospitals in the Region of Southern Denmark: the ED in Kolding, Lillebælt Hospital, the ED in Aabenraa, Hospital Sønderjylland, and the ED in Odense, Odense University Hospital. Six study assistants are associated to the study to ensure patient recruitment and data collection. They will be trained and certified in US of lung and kidneys (Objective Structured Assessment of Ultrasound Skills (OASUS) test), sputum collection, operation and integration of POC-PCR as well as POC urine flow cytometry.

Enrollment to the study commences from February 2021, and continues until the predefined sample size has been reached, which is estimated to be no longer than eight months. The last patient is expected to be enrolled in the end of September 2021. The patients will be enrolled from Sunday to Friday 10am-8pm except on holidays.

## Population and eligibility criteria

Mentally competent adults admitted to the ED will be invited to participate in the study, if the physician, receiving the patient, suspects the patient has an infection (e.g. indication for blood culture). If the physician at this moment suspects pneumonia, the patient will be offered additional diagnostics showed in track A in Figure 1. The physician will base his/her suspicion on e.g. clinical symptoms such as cough, increased sputum production, chest tightness, dyspnea and fever  $> 38^{\circ}\text{C}$ , and indication for chest x-ray (40).

Likewise, if the physician suspect pyelonephritis/urosepsis, the patient will be offered additional diagnostics showed in track B in Figure 1.

The exclusion criteria are:

- If the attending physician considers that participation will delay a life-saving treatment or if patient is transferred directly to intensive care unit (track A, B, and C)
- Patients which have been hospitalized within the last two weeks, to exclude hospital-acquired infections
- Only for patients with suspected pneumonia (track A)
  - o Patients  $< 40$  years and patient which have been included in the study once are excluded from the ULDCT and HRCT due to radiation risk
  - o Pregnant women due to radiation risk to the unborn child are excluded from the ULDCT and HRCT
  - o Patients treated with prednisolone 20 mg/d in the last two days will be excluded from POC-PCR analysis of sputum
- Only for patients with suspected pyelonephritis (track B)
  - o Common exclusion criteria for MRI e.g. pacemaker and claustrophobia
  - o Patients with known allergy to US contrast
  - o Pregnant women due to unknown impact of contrast to the unborn child

## Recruitment

Six appointed members of the research group will be study assistants (4 Ph.D. students and 2 one-year research medial students) will identify eligible patients through the local logistic system, and contact the emergency treating physician as early as possible after patient arrival. According to regional guidelines, a clinical assessment is performed within half an hour from arrival by the physician (41). According to the eligibility criterion the physician will assess whether the patient, has a suspected infection and if possible the focus of infection.

If the physician finds the patient eligible for inclusion, the patient will be contacted by a study assistant and informed about the study both verbally and in writing. The information will preferably be held in a patient room without presence of fellow patients. The patient will be offered up to 30 minutes consideration time if needed. The consideration time is set based that it is an acute condition which requires rapid treatment. The patient is allowed to have relatives present during the information and consideration. If the patient agree to participate, consent is obtained, which includes accept to collect blood samples for additional infection markers, collect urine for additional analysis, and collect health related data from the medical record from previous admissions, current admission and readmissions. If pneumonia is suspected, the consent also includes accept to bedside US, ULDCT, HRCT, and additional analysis of sputum. If pyelonephritis is suspected the consent also includes bedside US, advanced US, and MRI. If the patient does not wish to give consent to all parts of the study, consent can be given to individual parts.

The consent will be in writing, dated and signed. A copy of the signed consent will be attached to the participation information and handed out to the patient. For participants in isolation rooms, the consent form will not be collected physically for storage. A picture of the form will be taken and saved electronically in REDCap (Research Electronic Data Capture).

## Procedure

The procedure is illustrated in Figure 2. Upon arrival of potential participants, the study assistant contacts the nurse and ask her/him to wait to ordinate routine blood sample collection until the study assistant has invited the patient to participate in the study.

As soon as possible after recruitment (within half an hour from arrival), the study assistant will ordinate blood samples for routine blood culture and standard admission Workpackage (RBC, hemoglobin, monocytes, lymphocytes, WBC, WBC Differential Count, CRP, Sodium, Potassium, Calcium, Albumin, Creatinine, Uric Acid, Alkaline Phosphatase, GGT, Bilirubin, ALAT, LDH, INR, and Glucoses) and project samples.

The samples will be collected by a medical laboratory technologist. Urine sample for routine urine culture and POC urine flow cytometry will also be ordered, and collected by the study assistant. If the participants has suspected pneumonia, a sputum sample will be collected and analysed according to normal procedure. Some of the samples will be further analysed by POC-PCR and linked to a microbiological guidance. The study assistant also collects information about background, habitual and current symptoms through an interview with the patient. Above mentioned steps have to be performed within four hours after arrival.

If the participant has suspected pneumonia or pyelonephritis the study assistant will perform bedside US and ordinate ULDCT/HRCT or advanced US/MRI, respectively. The imaging will be performed within 24 hours after arrival.

During admission and after discharge, clinical, para-clinical and follow-up data will be collected from the medical record by the study assistants. All collected data will be entered in REDCap.

The procedure for the individual steps is described further in the next six subsections.

[figure not shown]

Figure 2 Defined procedure for data collection of enrolled patients

### Additional infection markers - PCT and suPAR

The blood will be collected in an 10mL EDTA tube. The samples will be transferred to the local laboratory for analysis. The results will be saved in a study database and not be visible for the physician in the medical journal.

#### Serum procalcitonin (PCT)

Serum PCT concentration is quantified with an automated sandwich immunoassay “ECLIA” (Elecsys, BRAHMS PCT-analyses) on Cobas e801. Calibration is performed after Cobas e pack has been registered in the instrument and is standardized to the BRAHMS PCT LIA assay. The correlation of Elecsys BRAHMS PCT analyses has been compared to BRAHMS PCT LIA and to BRAHMS PCT sensitive KRYPTOR with similar results of  $r=0.981$  and  $r=0.988$  respectively.

Serum PCT is tested within two hours from the collection of the blood sample. Quality control is performed after each calibration and regularly following the standard procedure. The manufacture states a lower limit of detection  $0.02 \mu\text{g/L}$  up to  $100 \mu\text{g/L}$ . The functional assay sensitivity is identified at  $\leq 0.06 \text{ ng/mL}$ . In this study a range from  $0.06 \mu\text{g/L}$  to  $100 \mu\text{g/L}$  will be measured. Normal healthy individuals have a PCT concentration  $< 0.1 \mu\text{g/L}$ . All plasma samples are screened for potential interfering substances like bilirubin, hemoglobin and lipids and no results will be included with significant interference. There is no hook-effect in PCT concentrations measured up to  $1000 \mu\text{g/L}$ .

The precision of PCT assay is expected to be <3% CV or similar. This is estimated from the internal quality controls using PC PCT1 (lot.419495) and PC PCT2 (lot.419497) at target PCT levels 0.49 and 9.44 ng/L showing a precision of 2.67 % CV and 2.63 % CV, respectively.

#### **Serum soluble urokinase plasminogen activator receptor (suPAR)**

Serum suPAR is measured using suPARnostic Tubilatex assay reagents (validated on Cobas c111) protocol for Cobas c702 and c502 applying the Multi-Pack cassettes (Roche Diagnostics, Mannheim, Germany) (42). Calibration is performed at least once a month or in connection to a new batch of TurbiLatex reagents, after calibration a quality control is performed. Serum suPAR is tested within two hours from the collection of the blood sample.

Measure range of the suPARnostic Tubilatex assay is 1.8 µg/L to 16.0 µg/L on Cobas c502 analyzer. The assay's limit of blank, limit of detection and limit of quantification are 1.0 µg/L, 1.2 µg/L and 1.2 µg/L respectively. Expected values for patients attending ED's range from 3-6 µg/L and can reach double digits in patients with severe disease related to poor prognosis. High concentration of SuPAR above 20 µg/L may be false positive results related with interference used by high concentration of hemoglobin, lipids or bilirubin. There is no identified interference in concentrations of bilirubin >350 µmol/L, triglycerides > 3.3g/L, hemoglobin > 1.4 g/L or rheumatoid factor > 440 IU/mL. The highest concentration of suPAR is tested at 47.5 µg/L without hook-effect and the linearity is from 1.8 µg/L to 26.6 µg/L. The mean value of precision of the test is 3.4 µg/L, 7.1 µg/L, 10.2 µg/L for low, middle and high concentrations of SuPAR respectively. The accuracy of suPARnostic Tubilatex is compared with suPARnostic ELISA with similar results < 15 % of difference.

The precision of suPAR assay is expected to be < 5% CV or similar. This is estimated from external quality assessment material, HK 19 (Product code 2226 DK, Lot. No. 201808) analyzed repeatedly during five different days on c502 and c702 and the mean content of suPAR determined by turbidimetry was 2.15 mg/ L and 2.03 mg/L (CV% 4.56 and 5.52) for the Cobas c502 and c702 instruments, respectively.

#### ***POC urine flow cytometry***

Within 4 hours from arrival, a urine sample will be collected according to routine procedure. The study assistant will be responsible for the collection to optimize compliance. Preferably a mid-ray urine or for catheter users (if possible) by introducing a clean catheter for optimal urine quality. The sample will be divided into two aliquots; one half for routine urine culturing in the Microbiological Department, and one half for POC urine flow cytometry analysis in the Biochemical Department.

The POC urine flow analysis is performed by the Sysmex UF -5000, a fully automated flow cytometry analyser for particle analysis in urine. It discriminates and counts 17 diagnostic parameters of cells and formed elements in urine. Particles are stained by specific flouorochromes for nucleic acids and for surface structures, and are exposed to a blue semi-conductor laser-light at 488 nm wavelength. Counting and classification is based on signals of forward scattered light (FSC), side scattered light (SSC), side fluorescent light (SFL), and depolarized side scattered light (DSS). The pattern of individual light signals is translated by algorithms allowing identification and classification into the particle categories, and results will be collected for bacteria, White Blood Cells (WBC), and Red Blood Cells (RBC). The light signals differ for Gram negatives and Gram positives, and this can be recognized by the analyser. For the above mentioned parameters, the analytical performance of the urine flow cytometer will be compared to the gold standard a urine culture on selective agar plates. A protocolled procedure for the collection and handling of samples will ensure consistent data quality.

The analysis will be carried out by laboratory assistants. The results of the POC urine flow cytometry analysis are not currently reckoned state-of-the-art and will be used for scientific purpose only. Results will be coded by the laboratory technician and not visible in the electronic laboratory system.

### ***Additional POC-PCR analysis of sputum if suspected pneumonia***

A sputum samples will be collected according to standard procedure as soon as possible after recruitment. The sample will be divided into two aliquots; one for routine sputum culturing by the Microbiological Department, and one for additional analysis.

The sample for additional analysis will be randomly assigned to one of two groups with 1:1 allocation:

1. Control: no POC-PCR will be done and no further intervention will be performed.
2. POC-PCR analysis linked to advice from microbiologist: Sputum samples will be analysed by the study assistant and results will be saved in the local microbiological database. The study assistant will tell a study microbiologist to contact the physician upon performing the 4-hour-treatment plan, and discuss optimal antibiotic treatment plan for the patient based on clinical sign and symptoms, chest X-ray, routine blood analyses and results from POC-PCR analysis.

The POC-PCR used in this study is by Biofire FilmArray Pneumonia Panel plus (Biomérieux, Marcy l'Etoile, France), which is a closed automatic system, nested multiplex PCR, that includes all the steps of molecular diagnostics, with running time of about 75 min, including sample preparation and nuclei-acid extraction. The panel includes 15 typical bacterial pathogens, three atypical bacterial pathogens, nine viruses and seven antimicrobial resistance genes. The results for typical colonizing bacteria are reported semi-quantitatively providing estimates to the nearest whole log as genome copies/ml ranging from  $10^4$  to  $10^7$  copies/mL, results from viruses, fungus and atypical bacteria are reported as "detected" or "not detected" and antimicrobial resistance genes are reported qualitatively in the case of simultaneous detection of a compatible pathogen. Testing of specimens using the panel will be conducted in accordance with the manufacturer's instruction (43). Each site will have a pocket laboratory protocol to ensure consistent data collection in quality and safe handling of specimens.

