### *Diagnostic value of bedside-US and ULDCT in diagnosing pneumonia*

The radiological findings will be described systematically using standardized assessment templates for US, ULDCT and HRCT. The project assistant will describe the bedside US findings, and radiologists will describe the ULDCT and HRCT diagnosis with standardized relevant clinical information. The US operators and the MRI-operator will be blinded to the results of each other. Study consultants with experience in lung imaging will post-process describe the scans and video clips systematically using developed research templates.

A reference diagnose for pneumonia is defined by a panel of experts. The experts are two consultants from Emergency Departments, who individually will determine if the diagnose was pneumonia, or not. The final diagnoses will be based on all available relevant information including e.g. results of imaging, blood sample and clinical information. A standardized template will be used. Disagreement will be discussed until a consensus is reached.

The results from bedside US and ULDCT of thorax are compared with HRCT of thorax and the reference diagnose. The advantages and disadvantages of the diagnostic capability of the individual modalities are described.

It is assumed that the reference diagnosis finds 98% of patients and index test 90%. With a power of 80%, at least 132 patients should be included (one-sided McNemar test).

The primary outcome is sensitivity and specificity, LLR+, LLR-, AUC for diagnosing pneumonia. To test the hypothesis a chi-squared test will be performed.

Secondary outcome will be sensitivity and specificity for chest x-ray. All outcomes will be reported with corresponding confidence intervals when relevant. Secondary analysis will compare sensitivity, specificity, ROC curve and AUC for ULDCT or bedside US compared to chest x-ray, using McNemar Chi-square to test the null-hypothesis

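### The bedside lung ultrasound operator is not blinded to the POC-PCR result, which the same staff role produces in one randomised arm

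*Protocol*

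**What the plan says.** **Who does what.** In the section on additional POC-PCR analysis of sputum, samples are "randomly assigned to one of two groups with 1:1 allocation"; in the POC-PCR group, "Sputum samples will be analysed by the study assistant and results will be saved in the local microbiological database". In Procedure, for suspected pneumonia or pyelonephritis, "the study assistant will perform bedside US and ordinate ULDCT/HRCT or advanced US/MRI, respectively". In the section on the diagnostic value of bedside-US and ULDCT, "The project assistant will describe the bedside US findings". Setting says "Six study assistants are associated to the study to ensure patient recruitment and data collection", and has these same people trained and certified in lung and kidney ultrasound and in operating the POC-PCR.

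**When.** After listing blood, urine, sputum, POC-PCR and the patient interview, Procedure says "Above mentioned steps have to be performed within four hours after arrival". For the scans it says "The imaging will be performed within 24 hours after arrival". The POC-PCR itself is described "with running time of about 75 min".

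**Blinding and readings.** The lung imaging section has one blinding sentence. It keeps the US operators and an MRI operator unaware of each other's results. Consultants later describe the stored scans and clips again. The index tests are compared with HRCT and with an expert-panel diagnosis that draws on all available relevant information. Sensitivity and specificity for pneumonia are primary outcomes.

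**The concern.** An index test should be read without knowledge of other tests that bear on the same diagnosis, unless the plan means to evaluate the combination. Here the person scanning may already hold a rapid pathogen result, and whether one exists is decided by randomisation. In the control arm there is no POC-PCR, so no such result exists at scan time.

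If the result colours how an equivocal scan is called, or which views are sought and stored, the pooled accuracy mixes two reading conditions: ultrasound with the PCR result known and ultrasound alone. The objective on the impact of bedside US in diagnosing pneumonia would then not be answered cleanly for ultrasound itself. The Protocol masks other study tests explicitly (PCT and suPAR are kept from the physician, and urine flow cytometry results are coded), but it has no comparable step here.

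**Working it through.** The Protocol states no figure on this point, so there is none to reproduce. The check is a reading of the sections against each other, followed by arithmetic for scale only.

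**1. Roles.** The assistant runs the POC-PCR (sputum section), performs the US (Procedure) and describes it (lung imaging section, under the title project assistant). Setting trains one group of six for both tasks across three EDs. No section separates the tasks, and none says that one individual does both for a given patient.

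**2. Timing.** The sputum and POC-PCR steps are due by 4 h and imaging by 24 h. If the PCR result is ready only at the 4 h limit, 24 − 4 = 20 h remain in which a scan made with the result known still complies. A scan before or during the run of about 75 minutes complies equally. The windows permit either order and prescribe neither.

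**3. Blinding.** The only sentence in the lung section pairs US operators with an MRI operator. The pneumonia track uses bedside US, ULDCT and HRCT, without MRI. The same sentence stands in the pyelonephritis section, where MRI is the reference scan. Neither place mentions POC-PCR.

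**4. Which reading counts.** There are two US readings, the assistant's and the consultants'. The section does not say which enters the accuracy analysis, or whether the consultants see the POC-PCR result.

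**5. Scale of a shift.** Let *d* be the change in US sensitivity caused by knowing the result, and *f* the share of scanned cases in the POC-PCR arm. The pooled shift is *f* × *d*. Allocation is 1:1, so *f* is at most about 0.5. It is lower if some scanned patients give no sputum, have no sample sent to randomisation, or are excluded from POC-PCR for prednisolone use. (The outcome section still mentions three randomisation groups; the sputum section and the amendment give two, which I use.)

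| Assumed *d* in POC-PCR arm | Largest pooled shift (0.5 × *d*) |
|---|---|
| 2 points | 1 point |
| 5 points | 2.5 points |
| 10 points | 5 points |

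The values of *d* are assumptions; the documents give none.

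**6. Direction.** Suppose a share *e* of scans is equivocal and is called in line with PCR, which agrees with the reference with probability *a*, where otherwise half would be called correctly. The change is *e* × (*a* − 0.5). With assumed *e* = 0.2 and *a* = 0.7 this is 0.2 × 0.2 = 4 points up. The sign depends wholly on *a*: below 0.5 among patients without pneumonia, specificity falls. The panel reports colonising bacteria semi-quantitatively and also detects viruses, so *a* among those patients cannot be taken from the documents.

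**7. Would a comparison by arm reveal it?** Assume 66 cases per arm (half of the 132 in the lung imaging section), 90% sensitivity in controls and a two-sided 5% test. With p̄ the mean of p₁ and p₂, power = Φ{[|p₁ − p₂|√n − 1.96√(2p̄(1 − p̄))] / √(p₁(1 − p₁) + p₂(1 − p₂))}.

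| Sensitivity in POC-PCR arm | Power |
|---|---|
| 92% | 6% |
| 95% | 19% |
| 98% | 49% |

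For 95%: (0.05 × 8.124 − 1.96 × 0.3725) / 0.3708 = −0.87, and Φ(−0.87) = 0.19. A null comparison would be little reassurance.

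**The case against.** The strongest reply is that the text shows only an opportunity for bias. Most of the reply stands, and it limits the point.

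- **Order.** A reader might infer that the scan always follows the PCR. The text does not say so: 4 h and 24 h are upper limits, and scanning during the run is already allowed. Figure 2, which illustrates the procedure, is not in the text available to me and may show a sequence.
- **Person.** A reader might infer that one individual does both tests in each patient. That is likely with six assistants over three sites, but it is not stated.
- **Second reading.** If the consultants' reading is the one analysed, the assistant's knowledge affects only image acquisition. This holds only if the consultants are themselves unaware of the PCR result, which is not stated.
- **Direction.** A reader might infer that accuracy is flattered by a few points. The documents do not support that. Detecting a coloniser or a virus is not the same as pneumonia, and US is also compared with HRCT. The focused scan looks for pneumothorax, effusion and interstitial syndrome on a standard template, where a pathogen result may have less pull than on a plain yes/no call for pneumonia.
- **Use in practice.** It cannot be said that future users would lack the PCR result, since the stated goal is one model combining all objectives. That does not remove the need to know what ultrasound contributes by itself.

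What survives is that no provision stops the operator from knowing the POC-PCR result, and that such a result exists in one arm only.

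**Conclusion.** The concern holds as a gap in blinding. One staff role generates the POC-PCR result in one randomised arm and performs and describes the bedside lung ultrasound. The time windows allow the second to be done with the first known, and the one blinding sentence does not address it and names a scan that this track does not use. A review bias that differs by arm is therefore possible in a primary accuracy outcome.

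Its size and direction cannot be established from the documents. Upward bias against the panel diagnosis is probable if the panel also sees the POC-PCR result, because test and reference would then share information; the Protocol neither includes nor excludes that. Against HRCT, or where PCR picks up colonisation, specificity could fall. The point figures above follow from assumed inputs and show scale only. Operator blinding is a matter of study conduct and cannot be restored in the analysis, so this is worth correcting in the Protocol, at moderate priority.

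**What to change.** 1. **Procedure and the sputum section:** require the assistant to record and lock the bedside-US template in REDCap before the POC-PCR result is opened, for example during the run of about 75 minutes, with time stamps for both. The lock should not hold back the PCR result; a scan not yet recorded by then is flagged. Use the same scan timing in both arms, because US findings are available to the treating physician and earlier scanning in one arm alone could affect the antibiotic comparison.
2. **Lung imaging section:** replace the MRI wording with a blinding statement that fits the pneumonia track. State which US reading, the assistant's or the consultants', is the primary index test, and that it is made without knowledge of the POC-PCR result.
3. **Analysis:** examine scans recorded after the result was known in a sensitivity analysis. Report accuracy by arm as description only, given its low power. Do not restrict the primary analysis by scan timing, since doing so in one arm may introduce selection.

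Cost: two time stamps, some rewording and a small constraint on the order of work; no extra tests or staff.
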